## Abstract

**Background::**

Prolonged post-operative ileus is associated with increased risk of other complications, length of hospital stays and health care related costs. Chewing gum has been shown to reduce duration of ileus in many elective surgeries, but there is a paucity of randomised controlled trials (RCTs) on its effect on duration of ileus among patients undergoing emergency surgery, specifically patients with peritonitis. The aim of this study is to determine the effect of chewing gum on duration of postoperative ileus following laparotomy for gastroduodenal perforations.

**Methods::**

This will be a randomised controlled trial done in 3 hospitals. Fifty-two patients will be randomised to 2 groups. Group A will receive chewing gum in addition to routine care, whereas group B will receive routine care only. The duration of post-operative ileus in the two groups which is the primary outcome, will be compared using the independent samples t-test in SPSS version 22. The length of hospital stay, in-hospital morbidity and mortality will be the secondary outcomes. This trial has been approved by Kampala International University research and Ethics committee (Ref No. **KIU-2021-60**) and Uganda national council of science and technology (Ref No. **HS1665ES**). Retrospective registration with the research registry has also been done (UIN: researchregistry8565).

**Highlights:**

## Introduction

Post-operative ileus (POI) occurs when gut motility briefly stops following surgery with no identifiable mechanical cause [1]. Prolonged postoperative ileus (PPOI) is the form that does not resolve by the 4^th^ post-operative day [2]. This form has been associated with prolonged admission time, high costs of health care and increased morbidity [3]. A study done to evaluate effect of POI in patients undergoing colectomy showed that the cost of prolonged POI was equivalent to the cost of re-admission with another adverse complication [4].

Over the years, patients who develop PPOI have been treated by passing a nasogastric tube (NGT), stopping oral intake and correcting electrolyte imbalances [3]. The currently available data shows that placement of a nasogastric tube does not prevent POI and may even increase the risk of other complications [5]. For this reason, the current recommendation is to avoid routine NGT insertion and to ensure early removal for those in whom it is deemed necessary [6]. Multiple preventive and treatment measures for POI have been studied over the years but the currently recommended measure is adherence to enhanced recovery after surgery (ERAS) protocols [5].

Chewing gum is reported to improve gut motility by activating the cephalic-vagal pathway that results in stimulation of gut myoelectric activity and intestinal movement [7]. This vagal stimulation is also thought to have an anti-inflammatory effect [8]. The first study that used chewing gum for POI resolution was done in 2002 among colon cancer patients [9]. This study reported reduced time to passage of stool, flatus and length of hospital stay [9]. Over the years more studies have been done in different study populations including laparoscopic, open, elective, emergency, colorectal, gynecological and many others with varying reports [1], [10,12].

The composition of chewing gum is chicle, a naturally occurring latex product [10]. Both sugar free and sugared chewing gum have been used [13,14]. The cost of PK, a sugared type of chewing gum (CG) is 250 Uganda shillings (0,065$) for a 5.6 g pack. The Ingredients of PK include sugar, gum base, glucose syrup, modified starch, emulsifier, soybean, lecithin, flavorings, glycerol, and an antioxidant (PK pack manufacture’s claim). In relation to the down sides of chewing gum, it cannot be given to patients that are not fully awake [15]. Also a sugared type of chewing gum has been reported to increase risk of dental curies [16], though rinsing and brushing regularly have been reported to mitigate this side effect [16,17].

Chewing gum has been studied in different settings of surgery including colorectal, appendectomy, Gynecological operations, caesarean section and some studies have involved different abdominal surgeries including both electives and emergencies [7,12,18,19,20]. One meta-analysis published in 2017 showed that in most of the studies done, patients were told to chew gum three to four times a day [21]. The duration for which patients chewed has been ranging from five to sixty munities as shown in one meta-analysis published in 2016 [22]. The quantity of gum chewed at each time has not been standard but statements like one stick, one pellet or two pellets have been used and in most studies patients usually start chewing within 24 hours after surgery when patient is fully awake [10,23].

### Rationale

There is paucity of data about treatment of POI and most of the medicines studied have had unsatisfactory outcomes [8]. For this reason most of the emphasis is currently on preventive management [21]. ERAS protocols have been proven to reduce POI duration in elective surgeries but data about such protocols in emergency surgeries is lacking [24]. The elements of ERAS recommended for reduction of POI in emergency surgeries, have been based on law risk patients [5,24], yet most of the patients in resource limited countries present late with a high risk of peritonitis and morbidity [25]. More so, some doctors avoid early feeding in fear of the complications since up to 20% of the patients do not tolerate it [11]. The minimally invasive surgery, a major component of ERAS is still a dream to most of the hospitals in resource limited countries. Most of the studies on chewing gum in POI were done in elective operations mainly colorectal. The mixed studies that included emergency operations, excluded patients that had gut perforations or peritonitis [7]. This study is necessary to understand if chewing gum can be effective in reducing postoperative ileus duration in patients with peritonitis.

### Study objectives

#### Main objective

The main objective in this trial is to determine the effect of chewing gum on duration of postoperative ileus following laparotomy for gastroduodenal perforations in a resource limited setting.

#### Specific objectives

To compare the time taken for post-operative ileus to resolve in the group of patients chewing gum versus the controls.To compare the duration of hospital-stay in the group of patients chewing gum versus the controls.To compare in-hospital morbidity and mortality in the group of patients chewing gum versus the controls.

### Hypotheses

The null hypothesis of this study is that there is no difference in the duration of POI when gum is chewed compared to when it is not.

## Methods

### Study design

This will be a multicenter prospective randomized controlled study with a parallel superiority design conducted in the surgical departments of Kampala International University Teaching Hospital (KIU-TH), Hoima regional referral Hospital (HRRH) and Fort portal regional referral Hospital (FRRH) in western Uganda. This work has been reported in line with the consort criteria [26].

### Study setting

HRRH has a bed capacity of about 600 with 3 general surgeons and 2 senior house officers. FRRH has a bed capacity of about 333 with 2 general surgeons and 3 senior house officers. KIU-TH has a bed capacity of about 700 with 6 general surgeons and 30 senior house officers. The surgery departments in the 3 study centers do both emergency and elective surgeries including the repair of gastric and duodenal perforations. The senior house officers do the operations under supervision of the general surgeons.

### Study population

All adult patients admitted to the surgical wards with a gastric or duodenal perforation during the study period will be targeted.

### Eligibility criteria

#### Inclusion Criteria

All patients with confirmed gastric or duodenal perforation, between the age of 18 and 65 will be included. The upper age limit will be used because increasing age increases the risk of PPOI [10] yet we want the groups to be comparable.

#### Exclusion Criteria

patients with documented allergies to the contents of chewing gumPatients with uncontrolled diabetes mellitus disease at the time of surgery since we are using a sugared type of chewing gum that may worsen the glycemic status.Patients who will be unconscious or unable to chew gum after 24 hours post-surgeryPatients with traumatic perforations will be excluded.

### Sample size estimation

Using the formula; 
N = 2\; \times \,{({\textstyle{{{Z_{1 - \alpha /2}}\; + {Z_{1 - \beta }}} \over \delta }})^2} \times {S^2}
 for determining sample size in randomized clinical studies with a statistical superiority design [27], and findings from a study that evaluated effect of chewing gum following pancreatic-duodenal surgery in Sweden [28], 46 participants per group will be required. On adjusting the sample size to the finite population and adding 10% to improve internal validity, the required sample size will be 52.

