### Data processing and analysis

The intention to treat model will be used during analysis to minimize bias. Summarized data will be analyzed using Statistical Package for the Social Sciences (SPSS Inc., Chicago, USA, version 22.0 for Windows). Continuous variables will be presented as the mean ± standard deviation. Categorical variables will be expressed as frequencies.

To compare the time taken for post-operative ileus to resolve and length of hospital stay, normality of distribution will be assessed using the Shapiro-Wilks test. If the data are found to be normally distributed, then equal variance for the two groups will be determined using Levene’s test hence two sample t-test will be computed assuming equal or unequal variance as appropriate. If the data are not normally distributed in both groups, the nonparametric Wilcoxon Rank sum (Mann-whitney U) test will be used to compare the difference in means. To compare the in-hospital morbidity and mortality, the chi squared test will be used. All analyses will be performed at 95% confidence level and a p value ≤0.05 will be considered significant.

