## Discussion

Previous researchers have not focused on acute peritonitis due to gastroduodenal perforations when assessing effect of chewing gum on ileus which this study is set to address. In their findings so far, there is compelling evidence to suggest that chewing gum plays a role in resolution of ileus [9,12], although controversial findings have been reported as well [28]. Our study is timely to shade more light in the context of low resource settings that are often under-represented in research publications.

Readily available and affordable chewing gum could offer benefit of reducing prolonged post-operative ileus and result in an added advantage of being discharged through a short-hospital-stay track. This protocol seeks to generate level one evidence regarding the role of chewing gum in resolution of ileus among patients with peritonitis due to gastro-duodenal perforations.

The generalizability of our study is limited by relatively smaller sample size and excluding patients with comorbidities but we hope our findings could be used to benchmark larger future multi center randomized controlled trials. More so, in this study, the participants will be un-blinded early since any placebo in this case would also count as sham feeding. We will only enroll patients with peritonitis due to gastroduodenal perforations which may not have a high bacterial burden compared to other gastrointestinal perforations thus generalizability of results will be limited in this context.

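### The stated requirement of 46 per group is cut to 52 in total by a finite-population correction that does not apply to a randomised comparison, so 52 is not the size that the protocol's own calculation requires

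*Protocol article*

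**What the plan says.** The Sample size estimation section of the protocol article gives the usual formula for comparing two means in a superiority trial, with Z(1-α/2) and Z(1-β), a difference δ and a standard deviation S. It takes planning values from a study of gum chewing after pancreatic-duodenal surgery and concludes that "46 participants per group will be required".

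The next sentence reduces this: "On adjusting the sample size to the finite population and adding 10% to improve internal validity, the required sample size will be 52". The size of the finite population is not given.

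The Abstract (Methods) shows that 52 is the total: "Fifty-two patients will be randomised to 2 groups". Allocation is 1:1 (section on sampling technique and randomization), so each group has 26.

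The Data processing and analysis section compares ileus duration with a two-sample t-test, or a Wilcoxon rank-sum test if the data are not normal, and "a p value ≤0.05 will be considered significant". Neither test is described as using a finite-population factor.

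**The concern.** Two consecutive sentences give two different requirements. The first needs 92 patients for the primary comparison. The second calls 52 the required number, and the step that removes 40 of them is a survey-sampling device.

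A finite-population correction is valid when the aim is to estimate a fixed quantity, such as a prevalence, in a closed list of people, and a large share of that list is sampled. The uncertainty then shrinks because few people are left unobserved. The aim here is the effect of a treatment, estimated from the difference between two randomised groups. Its standard error depends on the outcome variance and the number in each group, and the planned tests calculate it in that way. Patients dropped at the planning stage therefore reduce precision in the analysis, and nothing makes up for it.

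The stake is how the result is read. A reader who is told that the trial has its required size will take a non-significant result as evidence against chewing gum, although the chance of missing the planned effect may be between one third and one half.

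**Working it through.** **Inputs**

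- Required per group before adjustment: 46 (Sample size estimation).
- Final size: 52 in total, 26 per group (Sample size estimation; Abstract, Methods; 1:1 allocation).
- Significance level: two-sided 5% (p threshold in Data processing and analysis; Z(1-α/2) in the formula).
- Target power: not stated. Assumed to be 80%, with 90% as the upper end of the range.
- δ and S: not printed, so 46 cannot be recomputed from its inputs. It is taken as given.

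**Step 1. Can 52 be reproduced?**

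Without the correction: 2 × 46 = 92, and 92 × 1.1 = 101.2, so 102 (92/0.9 = 102.2, so 103).

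With the correction n/(1 + (n − 1)/N) and n = 92, a population of N = 96 gives 92/(1 + 91/96) = 47.2, and 47.2 × 1.1 = 52.0. Trying the usual forms of the correction and of the 10% addition, with rounding, 52 is reached for N of about 88 to 98. So 52 can follow from the steps described, with a population size that the article does not state. The number is arithmetically possible; the fault is in using the correction at all.

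**Step 2. Shortfall**

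26/46 = 57% of the requirement per group.

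**Step 3. Effect implied by 46 per group**

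Solving the protocol's formula for δ/S: d = (1.960 + z(power)) × √(2/46).

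- 80% planned: (1.960 + 0.842) × 0.2085 = 0.584 SD.
- 90% planned: (1.960 + 1.282) × 0.2085 = 0.676 SD.

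**Step 4. Power for that effect at the planned size**

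Normal approximation: Φ(d × √(n/2) − 1.960). With n = 26 and d = 0.584, this is Φ(2.106 − 1.960) = 55.8%. The t-test column uses the noncentral t distribution (50 degrees of freedom at 26 per group).

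| Planned power | Effect (SD) | 26 per group, normal | 26 per group, t-test | 23 to 24 per group, t-test |
|---|---|---|---|---|
| 80% | 0.584 | 55.8% | 54.2% | 49% to 51% |
| 90% | 0.676 | 68.3% | 66.6% | 61% to 63% |

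The last column assumes that about 10% of the 52 are lost. That is an illustration only, because the protocol does not describe its 10% as a loss rate.

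**Step 5. What 26 per group can show**

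- Difference detectable with 80% power (t-test): 0.79 SD, against 0.584 SD implied by 46 per group at the same power.
- Half-width of the 95% confidence interval: 2.009 × √(2/26) = 0.56 SD, nearly as large as the 0.584 SD effect.

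**The case against.** The strongest reply is that no arithmetic error is shown. As Step 1 demonstrates, 52 follows from 92 if the population is about 96, and a condensed article may leave that figure, along with δ, S and the target power, to the full protocol. This stands. Their absence is not part of the point, and the fault is one of method. It does not rescue the step, because a finite-population correction would be out of place here whatever N was.

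A second reply is that the Discussion admits a relatively small sample and looks ahead to larger trials. It does, but as a limit on generalizability. It does not say that the primary comparison falls short of its own calculation, and the Sample size estimation section still says "the required sample size will be 52".

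Several stronger readings are tempting, and the documents do not support them:

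- *Power is 54%.* This holds only if 80% was intended. No target power is stated, and 90% gives about 67%.
- *One group's number was mistaken for the total.* 46/0.9 = 51.1 does round up to 52, but the text describes a finite-population adjustment and a 10% addition. The coincidence proves nothing.
- *The planning study was a wrong choice.* The Discussion lists it among the controversial findings, but the article does not say which of its values were used, and using a study with contrary results is not in itself an error.
- *52 was set by feasibility.* No passage says so.
- *The evidence claim must be withdrawn.* The Discussion says "This protocol seeks to generate level one evidence regarding the role of chewing gum in resolution of ileus". This can refer to the randomised design rather than to power, and rewriting the aim is a matter of preference.

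**Conclusion.** The point holds. By the protocol's own formula the trial needs 46 per group, 92 in total. The planned 52 gives 26 per group, and the correction used to get there does not apply to a randomised superiority comparison or to the planned tests. The statement that 52 is required is therefore wrong as written.

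For the effect implied by 46 per group, at two-sided 5% and with all 52 evaluable, t-test power is about 54% if 80% was planned and about 67% if 90% was planned, and lower with any losses. The difference detectable with 80% power is about 0.79 SD. These figures take 46 as correctly calculated and rest on the t-test; power of the rank test would depend on the shape of the data. In both cases power is well below target, so the conclusion does not depend on which target was meant.

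**What to change.** In Sample size estimation, delete the finite-population step and the statement that 52 is the required size. State instead that the formula requires 92 in total, about 102 with the 10% addition, and that the planned 52 falls short of this. Give the power of 52 for the planned difference (about 54% if 80% was the target, about 67% if 90%) and the difference it can detect with 80% power (about 0.79 SD).

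Add that a non-significant primary result will be interpreted from the 95% confidence interval for the difference and will not be taken as evidence of no effect.

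The cost is wording and a less favourable stated power. The restatement needs no extra patients and no change to the planned tests.

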### Sampling technique, randomization, concealment allocation and blinding

Permuted balanced block randomization will be conducted by the study supervisor to generate a random sequence of numbers to represent the two groups in an equal allocation ratio of 1:1. The random numbers will be labeled on concealed envelopes. The sealed envelopes will contain a folded opaque paper with letter A or B representing (chewing plus routine care) and (non-chewing plus routine care) groups respectively so that its not possible to deduce the assignment group based on random sequence numbers by the allocating team (research assistants). In addition, the envelope will have a similar stamp on the seal to be able to deduce possibility of breach of protocol (premature opening of the envelope). At this time both consent for surgery, information about the study and or consent to participate in the study will be obtained in writing at the emergency department. This is to avoid bias of recruiting participants after knowledge of intra-operative findings and to enable pre-operative care standardization between groups. The allocating team (trained research assistants) will give the envelope to the eligible participant 2 hours prior to surgery when a diagnosis of gut perforation is made from the radiological findings. The envelope will remain sealed until the patient enters the operating room and the participant will be unblinded just before induction of anesthesia where an instruction will be issued regarding chewing or not chewing any gum post-operatively. At this point an additional number either H, F or K will be added to the sequence number on the envelope to form participant identification number (PIN) to represent HRRH, FRRH, KIUI-TH for tracking records of recruitment and representation from each hospital. The outcome assessors (attending physicians) will be blinded throughout about the ongoing study since chewing gum is not known to cause adverse effects that would warrant un-blinding. The recruiting team will be totally different from the outcome assessors.

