### Participant recruitment and study procedure

Patients admitted in emergency department (ED) with suspected gastric or duodenal perforation based on clinical and radiological assessment will be evaluated for eligibility and considered as possible candidates for the study.

Routine pre-operative management for GDP will be done for all patients including; taking vital signs like; Blood pressure (BP), pulse rate (PR) respiratory rate (RR), oxygen saturation (SPO2) and temperature plus continuous monitoring, passing Foley’s urethral catheter and monitoring urine output, passing two large bore cannulas, fluid resuscitation with IV Normal saline till urine output is >0.5 mls/h, nasogastric tube insertion, nil by mouth, intravenous (IV) ceftriaxone 2 grams (g), IV metronidazole 500 milligrams (mg), IV Paracetamol 1g, IV omeprazole 40 mg, doing complete blood count (CBC), doing blood grouping and cross match, serum electrolytes, and obtaining informed consent for emergency laparotomy.

After resuscitation, the patients will be taken for laparotomy under intubation general anesthesia. Patient’s particulars will be recorded in the data collection form including participant identification number (PIN), age, address, presenting symptoms and duration of symptoms among others as shown in appendix I. The type of perforation surgery will be recorded.

Post operatively patients in both groups will receive all the routine post-operative care. This will include IV Normal saline and 5% dextrose in the ratio of 2:1, which will be prescribed for the first 24 hours with the total volume determined by the 4:2:1 rule for calculating maintenance fluids. The fluid prescriptions that follow, will be according to fluid balance chart. Other post-operative instructions will include; IV ceftriaxone 2g once a day (OD) for 5 days, IV metronidazole 500mg 8 hourly for 5 days, IV Omeprazole 40mg OD till oral feeding is initiated, IV Paracetamol 1g 8 hourly till oral feeding is initiated, Oral warm water will be started on first POD, early removal of NGT will be done, ambulation will be encouraged from first POD [14,25]. In addition to the above, patients in group A will receive chewing gum and below is a clear instruction on how they will use it. Figure 1 shows a flow chart summarizing the study procedure.

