### Chewing gum administration

Green PK brand of chewing gum will be used in this study since a pilot survey done before data collection showed that majority of the people preferred the green flavor (*appendix II, unpublished data*). We will use one flavor to minimize bias. The patients in Group A will be given green flavored PK and will start chewing after regaining consciousness. The patients will chew 2 pellets of PK till they are tasteless three times in a day (morning, afternoon, and evening). After chewing, the patients will be encouraged to rinse the mouth with clean water. The patients will stop chewing gum when POI resolves. Resolution of POI will be defined as passage of stool or flatus or both in addition to full filling the criteria defined in the 6 domains described by the Tripartite gastrointestinal recovery post-operative ileus group such as absence of nausea and vomiting, having no need of nasogastric intubation, absence of abdominal pain and distension, and ability to tolerate oral feeds [29]. Each patient will be offered a watch, notebook, and pen and with the help of the caretaker, record every day’s events and the time they occur. The events recorded will include; time when gum is chewed, flatus passed, stool passed, vomited or hunger felt. The outcome assessors will do clinical evaluation 6 hourly and information will be recorded in the data collection form (appendix I).

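### Allocation is opened before laparotomy, but the 24-hour chewing exclusion, and probably confirmation of the perforation site, can only be settled afterwards, which conflicts with the intention-to-treat analysis

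*Protocol article*

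**What the plan says.** The sequence is spread over several sections of the Protocol article.

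- **Recruitment** (Participant recruitment and study procedure): patients "with suspected gastric or duodenal perforation based on clinical and radiological assessment will be evaluated for eligibility".
- **Handing over the envelope** (Sampling technique, randomization, concealment allocation and blinding): the task of the research assistants is described thus: "will give the envelope to the eligible participant 2 hours prior to surgery when a diagnosis of gut perforation is made from the radiological findings". No site of the perforation is mentioned at this step.
- **Opening the envelope** (same section): "The envelope will remain sealed until the patient enters the operating room and the participant will be unblinded just before induction of anesthesia". The instruction to chew or not to chew is given then.
- **Inclusion Criteria**: "All patients with confirmed gastric or duodenal perforation, between the age of 18 and 65 will be included".
- **Exclusion Criteria**: patients who are "unconscious or unable to chew gum after 24 hours" post-surgery are excluded.
- **Start of gum** (Chewing gum administration): group A "will start chewing after regaining consciousness".
- **Analysis** (Data processing and analysis): intention to treat.

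The reason given for approaching patients before surgery is: "This is to avoid bias of recruiting participants after knowledge of intra-operative findings and to enable pre-operative care standardization between groups".

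**The concern.** An eligibility rule should be settled before the arm is known. Here at least one rule is applied about a day after the envelope is opened, so the set of patients compared can depend on the arm.

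The chewing criterion is the sensitive one. A group A patient who cannot chew shows it at once, because chewing is the treatment. A group B patient is told not to chew, and no chewing assessment is described for that group. Patients who cannot chew a day after surgery are plausibly the sickest, with the longest ileus. If they leave group A more often than group B, mean ileus time in group A becomes shorter without any effect of gum.

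The site criterion raises a different problem. A patient found at laparotomy to have a perforation elsewhere uses up one of the 52 allocations. Nothing links this to the arm, so the expected cost is numbers rather than bias.

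**Working it through.** **1. Order of events**

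| Step | Time | Known at that point |
|---|---|---|
| Consent, screening | Emergency department | Perforation suspected |
| Envelope handed over | 2 hours before surgery | Gut perforation on radiology |
| Envelope opened | Before induction | The same, plus the arm |
| Laparotomy | After opening | Site seen directly |
| Chewing exclusion | After 24 hours post-surgery | Whether the patient can chew |

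The last row alone establishes the conflict, since it necessarily follows the third. The site criterion probably does too: the text does not define confirmation, and the radiological trigger does not name a gastroduodenal site.

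**2. Effect size implied by the plan**

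The Sample size estimation section gives 46 per group but no difference, SD or power, so 46 cannot be reproduced. Solving its formula backwards, with two-sided alpha 0.05 and power *assumed* to be 80%:

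d = √(2 × (1.960 + 0.842)² / 46) = 0.584 SD.

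**3. Cost in numbers**

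Power of the two-sample t-test (noncentral t) at d = 0.584, with an assumed fraction f of the 52 lost after allocation:

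| f | Analysed, 52 × (1 − f) | Power |
|---|---|---|
| 0 | 52 | 54% |
| 10% | 46.8 | 50% |
| 20% | 41.6 | 45% |
| 30% | 36.4 | 40% |

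**4. Bias from unequal exclusion**

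Assume that gum has no effect, that a fraction p of each arm cannot chew, and that their ileus is L SD longer. All such patients are dropped in group A and a fraction g of them in group B. The mean of those left in B then exceeds the mean of those left in A by

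bias = L × p(1 − g) / (1 − pg), in favour of gum.

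- g = 0, p = 0.10, L = 1: 1 × 0.10 = 0.10 SD.
- g = 0, p = 0.15, L = 2: 2 × 0.15 = 0.30 SD.
- g = 0.5, p = 0.10, L = 1: 0.05 / 0.95 = 0.05 SD.
- g = 0.5, p = 0.15, L = 2: 2 × 0.075 / 0.925 = 0.16 SD.
- g = 1: 0 in every case.

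Two-sided type I error of the nominal 5% t-test, simulated with 26 per arm before exclusions and normal data:

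| Dropped in B | p = 10%, L = 1 | p = 15%, L = 2 |
|---|---|---|
| None | 6% | 13% |
| Half | 5% | 7% |
| All | 5% | 5% |

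The values of p, L, g and f are assumptions; none comes from the protocol.

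**The case against.** Several stronger readings are tempting, and the text does not support them.

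- *Every eligibility criterion is settled too late.* Traumatic perforation has no stated time of assessment, and the history may settle it in the emergency department. Radiology may also be what is meant by confirmation, although at the allocation step it supports only a gut perforation.
- *Intention to treat is abandoned.* The protocol states intention to treat and never says that wrong-site patients leave the analysis. The Termination from the study section concerns non-adherence, cross-over and loss to follow-up, not ineligibility found later. Figure 1 is not shown and may say more. What stands is that the Exclusion Criteria and the analysis section are not reconciled.
- *The criterion will be applied unequally.* One rule is stated for both arms, and unconsciousness is equally visible in both. Unequal use is a risk, not a stated fact. Blinding of the outcome assessors does not remove it, because the bias comes from who remains in the comparison and the text does not say who decides the exclusion.
- *The operating team learns the arm.* The text says that the participant is unblinded and instructed; it does not say who else sees the paper.
- *Late exclusions explain the low power.* Most of the fall, from the assumed 80% to 54%, comes from reducing 46 per group to 52 in total, which is a separate matter. Losing 10–30% takes off a further 4–14 points.

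The early approach also has a purpose: to prevent recruitment in the light of operative findings and to standardise pre-operative care. Consent before surgery already serves that purpose. It does not require the arm to be opened before laparotomy.

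**Conclusion.** The point stands in this form. The chewing exclusion certainly post-dates open allocation, and confirmation of the site probably does. Applying the exclusion as written removes randomised patients after the arm is known and conflicts with intention to treat.

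Confidence is high on the timing and much lower on the size. The 0.30 SD upper figure, about half of the implied 0.584 SD effect (0.30 / 0.584 = 51%), requires exclusion in group A only. The bias falls to 0.05–0.16 SD if half of such patients are also dropped in group B, and to nil under equal application. The power figures rest on the assumed 80% design power. The change is nevertheless worth making, because it removes the problem whatever the true rates are.

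**What to change.** Keep consent before surgery. Open the next numbered envelope only after surgery, once the operative note confirms a gastric or duodenal perforation and the patient is awake and able to chew within the 24-hour window. Log consented patients who fail these checks as not randomised, and count the 52 from that point. Gum is not started before consciousness returns, so the intervention does not depend on opening the envelope earlier.

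The cost is modest. The same envelopes and research assistants are used, but more patients must be consented than are randomised, and assistants must be available at three hospitals when patients wake.

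Registration was retrospective, so some envelopes may already have been opened. Keep every such patient in the intention-to-treat analysis, report later ineligibility by arm with reasons, and amend the Exclusion Criteria so that they agree with the analysis section.
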